### Study Protocol

Eligible patients will be centrally randomized 1:1 to receive either warfarin or rivaroxaban using a study-specific electronic case-report form management system. Patients randomized to the rivaroxaban group will receive rivaroxaban 20 mg orally once daily; those with an estimated glomerular filtration rate of 30–49 mL/min/1.73 m^2^, determined using the Chronic Kidney Disease Epidemiology Collaboration (CKD-EPI) equation, will receive 15 mg. Patients randomized to the warfarin group will receive warfarin 3 mg once daily for two consecutive days (2 mg once daily in patients with the body weight of <50 kg), followed by an appropriate dose once daily prescribed by the investigator at each center according to the patients' prothrombin time. The target INR is 2–3, and low molecular weight heparin (enoxaparin, 1 mg/kg every 12 h) will be administered until the INR of participants reaches 2. All randomized patients will receive standard-of-care for HF management during index hospitalization and follow-up period of 180 days after discharge. Following randomization, HF and any other comorbidities will be managed appropriately. However, anticoagulation with any drugs other than the study treatments will be avoided.

Patients will be assessed periodically at pre-specified study visits during hospitalization [visits 1 (day 1), 2 (day 2), 3 (day 4), and 4 (day 7 or discharge, whichever occurs first)] and after hospitalization [visits 5 (discharge day 30), 6 (discharge day 90), and 7 (discharge day 180)] (Figure 1). Vital signs, and HF signs and symptoms will be assessed according to the New York Heart Association functional class and visual analog scale for dyspnea from discharge to day 180 (Table 3). Additionally, adverse events will be recorded at all visits.

**Table 3 T3:** Assessment schedule.

**Time point**	**In-hospital visits**				**Post-discharge visits**		
	**Visit 1**	**Visit 2**	**Visit 3**	**Visit 4**	**Visit 5**	**Visit 6**	**Visit 7**
	**D1**	**D2**	**D4**	**DC 0 (or D7)**	**DC30 ± 7D**	**DC 90 ± 7D**	**DC 180 ± 7D**
Screening procedures	•						
Medications^*^	•			•			•
Vital signs	•	•	•	•	•	•	•
Physical examination	•	•	•	•	•	•	•
Evaluation of congestion^†^	•	•	•	•	•		•
Height, body weight	•	•	•	•	•	•	•
Prescription of study drug	•			•	•	•	
Laboratory tests (local)	•	•	•	•	•	•	•
Laboratory tests (central)	•	•	•	•	•		•
Human-derived materials	•	•	•	•	•		•
HF symptoms (VAS, NYHA class)	•	•	•	•	•		•
Electrocardiography	•	•	•	•	•	•	•
Chest X-ray	•				•	•	•
Assessment of adverse events	•	•	•	•	•	•	•
Assessment of clinical outcomes	•	•	•	•	•	•	•

*D, day; DC, discharge day; NYHA, New York Heart Association; VAS, visual analog scale*.

* *The following medications taken by a patient within ~24 h prior to screening will be collected: aspirin, clopidogrel, warfarin, angiotensin converting enzyme inhibitor (ACEI), Angiotensin II Receptor Blocker (ARB), beta blocker, ivabradine, entresto, statin, omega 3 fatty acid, furosemide, torsemide, spironolactone, hydrochlorothiazide, thiazide-like, other diuretics, thiazolidinedione (TZD), Dipeptidyl-peptidase 4 (DPP4) inhibitor, metformin, sulfonylurea, Sodium-glucose transport protein 2 (SGLT2) inhibitor, insulin, dronedarone, other anti-arrhythmics. The following concomitant medications at discharge will be collected: aspirin, clopidogrel, warfarin, ACE I, ARB, beta blocker, ivabradine, sacubitril/valsartan, statin, omega-3 polyunsaturated fatty acids, furosemide, torsemide, spironolactone, hydrochlorothiazide, thiazide-like, other diuretics, TZD, DPP4 inhibitor, metformin, sulfonylurea, SGLT2 inhibitor, insulin*.

† *Evaluation parameters are as follows: tachypnea, rales, S3 gallop, edema, orthopnea, bendopnea, neck vein engorgement*.

Blood will be collected locally at pre-specified visits and analyzed for biomarkers and end-organ function. A detailed list of hematology, chemistry, and coagulation assessments is presented in Table 4. Biomarker analyses will be performed in a central laboratory. A subset of blood chemistry tests, including blood urea nitrogen, creatinine, electrolytes (Na^+^, K^+^, Cl^−^), and liver enzymes (serum alanine aminotransferase and aspartate aminotransferase) will be repeated by the central laboratory to confirm the accuracy of the laboratory data from local centers. If there is a discrepancy in blood chemical tests between the central laboratory and local centers, the results from the central laboratory will be used for the analysis. Blood samples will be stored for future biomarker analyses. Electrocardiograms will be obtained and interpreted locally at each visit and sent to a central laboratory for evaluation.

**Table 4 T4:** Hematology, chemistry, and coagulation assessments.

**Category**	**Lists**
Hematology	White blood cell count, red blood cell count, hemoglobin, hematocrit, platelet, mean corpuscular volume, red cell distribution width, neutrophil count, and lymphocyte count
Chemistry	Calcium, inorganic phosphate, fasting glucose, uric acid, cholesterol, total protein, albumin, alkaline phosphatase, total bilirubin, serum alanine aminotransferase, aspartate aminotransferase, sodium, potassium, chloride, blood urea nitrogen, and creatinine
Coagulation	Prothrombin time (INR)
Urine lab	Specific gravity, pH, protein, glucose, ketone, red blood cell, urobilinogen, bilirubin, nitrite, and white blood cell

*INR, international normalized ratio*.

### Statistical Considerations

#### Sample Size

Data on hsTn in patients with ADHF and AF after anticoagulation treatment are lacking. However, hsTn was studied as a potential biomarker in patients with ADHF in the RELAX-AHF trial of serelaxin (18, 19). As the hsTn level is related to ADHF, information on hsTn from RELAX-AHF can be used, based on the following assumptions. Based on a feasibility assessment, 150 patients (75 patients in each treatment group) are planned for enrolment. In the RELAX-AHF study, the geometric mean of hsTn at the baseline and 95% confidence interval (CI) was 0.034 (0.032–0.037), with 581 patients. Therefore, assuming the log-scaled standard deviation is 0.75, with a sample size of 75 patients, the maximum imprecision of the geometric mean is 18%, which is considered to provide reasonable precision of estimate. The rate of drop-out is not considered in the calculation as the primary endpoints will be evaluated during hospitalization, and the drop-out rate is anticipated to be very low.

#### Analyses

As the current study is not powered for clinical hypothesis testing, statistical analyses will be explorative and descriptive. All variables will be analyzed descriptively: categorical variables will be presented as frequency tables (absolute and relative frequencies with 95% CI) and continuous variables by summary statistics (mean, standard variation, minimum, median quartile, and maximum, and 95% CI). We will analyze circulating hsTn and other quantitative biomarkers with natural log-transformation, and the geometric mean with 95% CI will be provided for each visit. The adjusted geometric means of the maximum change in hsTn from the baseline to hospitalization will be evaluated using an analysis of covariance model, with the value at admission as a covariate, and stratification factors used for randomization and treatment as a factor. The treatment geometric mean ratio, which reflects the treatment difference between rivaroxaban and warfarin, as well as its 95% CI, will also be provided.

A survival analysis will be performed to describe the time from hospital admission to the composite endpoint, including all-cause mortality and rehospitalization. Kaplan–Meier estimates and plots will be obtained for each treatment. The hazard ratio for rivaroxaban over warfarin and its 95% CI will be generated from the Cox-proportional model. The incidence of all-cause mortality during hospitalization will be summarized in a frequency table with the corresponding percentage and 95% CI. The incidence of major and minor bleeding events during the study will be summarized in a frequency table with percentage and corresponding 95% CI. To adjust variations in treatment duration during the study, the incidence rate (number of patients with bleeding events divided by the cumulative person-time on treatment) will also be provided.

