### Objectives and Endpoints

The primary study objective is the maximum change in the hsTn level over 72 h from admission following treatment (Table 1). The maximum change in hsTn is defined as the greatest change from the natural log-transformed baseline hsTn value to the natural log-transformed peak hsTn value during hospitalization. The secondary objectives are the: (1) change in the hsTn level 30 and 180 days after treatment with rivaroxaban or warfarin [target international normalized ratio (INR): 2–3]; (2) change in D-dimer level during and after hospitalization as a thrombogenicity marker; (3) change in other biomarkers of cardiac fibrosis [soluble ST2 (sST2) and galectin-3], renal injury [cystatin C, neutrophil gelatinase-associated lipocalin (NGAL), and N-acetyl-β-D-glucosaminidase (NAG)], and thrombogenicity [thrombin–antithrombin (TAT) complex and plasminogen activator inhibitor type 1 (PAI-1)], hs-CRP, and NT-proBNP during and after hospitalization; (4) incidence and rate of major bleeding according to the International Society on Thrombosis and Haemostasis criteria (16) (e.g., bleeding causing a decrease in hemoglobin level of ≥2 g/dL; bleeding leading to transfusion; symptomatic bleeding in critical areas including intracranial, intraspinal, intraocular, pericardial, intraarticular, intramuscular with compartment syndrome, and retroperitoneal; and fatal bleeding causing death) or minor bleeding event during and after hospitalization; (5) hospital stay duration at initial hospitalization; (6) incidence of all-cause mortality during hospitalization and at 180-day follow-up; and (7) incidence of all-cause mortality and rehospitalization during hospitalization and at 180-day follow-up.

**Table 1 T1:** Study endpoints.

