**Secondary endpoint**
• Change in hsTn from the baseline following hospitalization and 30 and 180 days after treatment with rivaroxaban or warfarin • Change in D-dimer from the baseline during and after hospitalization (Days 2, 4, and 7 or discharge, and 30 and 180 days after discharge) • Change in other biomarkers, including TAT complex, PAI-1, hs-CRP, NT-proBNP, sST2, galectin-3, cystatin C, NGAL, and NAG from baseline during (Day 7 or discharge) and after hospitalization (30 and 180 days after discharge) • Incidence and rate of major/minor bleeding events during and after hospitalization • Length of hospital stay at initial hospitalization • Incidence of all-cause mortality during and after hospitalization • Incidence of all-cause mortality and rehospitalization during the 180-day follow-up

*hsTn, high-sensitive troponin; TAT, thrombin–antithrombin complex; PAI-1, plasminogen activator inhibitor type 1; hs-CRP, high-sensitivity C-reactive protein; NT-proBNP, N-terminal proBNP; sST2, soluble ST2; NGAL, neutrophil gelatinase-associated lipocalin; NAG, N-acetyl-β-D-glucosaminidase*.

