### Justification for the Extended Therapeutic Intervention and Follow-Up

Studies on the efficacy of novel target drugs, such as ularitide or serelaxin, during short-term hospitalization reported unsatisfactory long-term outcomes in patients with ADHF (24, 25). Furthermore, the results of the ASTRONAUT study, which investigated the change in Tn between the pre- and early post-discharge periods (1 month) in hospitalized patients with ADHF, demonstrated that patients experienced an extended period of vulnerability to cardiac injury after the index hospitalization (26). Therefore, in our study, anticoagulation evaluation in both rivaroxaban and VKAs groups will be continued for 6 months, and the long-term effect will be assessed as a secondary outcome. For example, the serial changes in hsTn and clinical outcomes will be followed up to 6 months. The extended treatment and follow-up assessments are expected to elucidate the long-term efficacy and safety of rivaroxaban. Furthermore, we will evaluate the clinical effect of changes in hsTn during hospitalization and early-discharge on long-term clinical outcomes.

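### The bleeding rate counts each patient once but divides by all on-treatment time, and does not say that only on-treatment bleeds are counted

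*Protocol article*

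**What the plan says.** The Analyses section of the protocol article plans two bleeding summaries. The first is a table of proportions: "The incidence of major and minor bleeding events during the study will be summarized in a frequency table". The second is a rate: "the incidence rate (number of patients with bleeding events divided by the cumulative person-time on treatment) will also be provided". Its stated purpose is "To adjust variations in treatment duration during the study".

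Objectives and Endpoints lists bleeding as secondary objective (4), with both an incidence and a rate. Table 1 words the endpoint as "Incidence and rate of major/minor bleeding events during and after hospitalization". Under Study Protocol, "adverse events will be recorded at all visits", the last visit being 180 days after discharge. Treatment is meant to run as long: "anticoagulation evaluation in both rivaroxaban and VKAs groups will be continued for 6 months" (Justification for the Extended Therapeutic Intervention and Follow-Up).

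The Analyses section calls the analyses exploratory and descriptive. It plans no test and no rate ratio for bleeding.

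**The concern.** A rate of first events needs a numerator and a denominator that cover the same time at risk. Here they can come apart in two ways.

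- **Time after the first bleed.** A patient who bleeds and stays on treatment goes on adding time to the denominator but can add nothing more to the numerator. This follows from the formula as written and lowers the rate, more so in the arm with more bleeding.
- **Bleeds after stopping.** Only the denominator is restricted to treatment. The neighbouring sentence and the endpoint wording cover the whole study. If a bleed after the end of treatment is counted, it enters the numerator while the time in which it arose is left out. This raises the rate, more so in the arm with more discontinuation.

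The rate is there to make arms with different treatment durations comparable. The first problem makes an excess of bleeding look smaller. The second lets a difference in discontinuation look like a difference in bleeding. The study is open-label, so discontinuation may differ by arm.

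**Working it through.** The article gives no bleeding rate, no discontinuation rate and no rate ratio, so there is no figure of its own to reproduce. The 75 patients per arm come from Sample Size and the 180 days after discharge from Study Protocol. All risks, discontinuation proportions and hazards below are assumptions.

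**1. Time not stopped at the first bleed.** Assume a constant hazard, 187 days (180 plus an assumed 7 in hospital), no discontinuation and no deaths. T = 187/365.25 = 0.512 years, and p is the proportion of patients who bleed.

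- Plan: p/T. Time stopped at the first bleed: −ln(1−p)/T.
- p = 15%: 0.15/0.512 = 0.293 against 0.1625/0.512 = 0.317 per patient-year. 0.293/0.317 = 0.92, about 8% too low.
- p = 25%: 0.25/0.512 = 0.488 against 0.2877/0.512 = 0.562. 0.488/0.562 = 0.87, about 13% too low.
- Implied ratio: 0.488/0.293 = 1.67 against 0.562/0.317 = 1.77.

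For a patient who stops at the bleed, treatment time ends with the event and this error disappears. The figures are therefore the case in which every bleeder continues.

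**2. Off-treatment bleeds in the numerator.** Assume 180 days, the same 10% bleeding risk in both arms while on treatment (true ratio 1.00), exponential discontinuation reaching 10% in arm A and 30% in arm B, and an off-treatment hazard k times the on-treatment hazard.

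- Mean treatment time with discontinuation d is 180·d/(−ln(1−d)). Arm A: 18/0.1054 = 170.8 days. Arm B: 54/0.3567 = 151.4 days.
- True rate: 0.1054/(180/365.25) = 21.4 per 100 patient-years in both arms.
- At k = 1, 10% of each arm bleeds. Arm A: 0.10/(170.8/365.25) = 21.4. Arm B: 0.10/(151.4/365.25) = 24.1. The ratio equals 170.8/151.4 = 1.13.

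| Off-treatment hazard (k) | Arm A | Arm B | Apparent ratio |
|---|---|---|---|
| 1 | 21.4 | 24.1 | 1.13 |
| 0.5 | 20.9 | 22.3 | 1.07 |
| 0.25 | 20.6 | 21.3 | 1.04 |
| 0 | 20.3 | 20.4 | 1.00 |

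Rates are per 100 patient-years. At k = 1, arm A matches the true rate only because the two errors cancel there. With equal discontinuation in the two arms the ratio is 1.00.

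**3. Does the repair work?** In the same scenario, on-treatment bleeds over all on-treatment time give 20.3 and 20.4, ratio 1.00. Stopping time at the first bleed as well gives 21.4 in both arms, which is the true rate.

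**4. Sampling error.** The 95% limits of a rate ratio are a factor exp(1.96·√(1/a+1/b)) each way, with a and b the numbers of patients who bleed.

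- 10% in each arm: a = b = 7.5, so exp(1.96·0.516) is about 2.7.
- 15% and 25%: 11.25 and 18.75, so exp(1.96·0.377) is about 2.1.

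Both are far larger than a shift of 1.77 to 1.67 or of 1.00 to 1.13.

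**The case against.** The strongest reply is that the formula gives no window for its numerator. The whole-study wording belongs to the sentence on the frequency table. The rate is introduced separately as an adjustment for treatment duration, which fits on-treatment bleeds at least as well. The phrase in Table 1 separates hospital from post-discharge time, not time on drug from time off drug, and with six months of planned treatment most post-discharge bleeds would be on treatment. At-risk windows and censoring rules are ordinary content for a full protocol or analysis plan, and neither is shown.

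Much of this stands. A reader might infer that the plan definitely counts bleeds after stopping. The article neither says so nor excludes it, so the second problem is conditional.

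The reply does not dispose of the first problem. The article states both parts of the formula: patients in the numerator, cumulative treatment time in the denominator. That is a stated rule and not merely an omitted detail, and followed literally it understates each arm's rate. An unseen plan may refine it, but the published definition needs correcting.

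It is also fair to say that the error is small when bleeding is rare. At a 5% risk, 10.2 against 10.4 per 100 patient-years is hardly visible.

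**Conclusion.** The point holds as a minor defect in a stated definition. The understatement follows from the formula whenever patients continue treatment after a bleed. The inflation needs two things together: off-treatment bleeds in the numerator and unequal discontinuation. The sizes rest on constant hazards and on bleeding and discontinuation figures that the article does not supply.

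Three stronger readings are tempting and are not supported.

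- **That the trial will report a false rate ratio.** None is planned. What is exposed is an informal comparison of two descriptive rates, and the Limitations section says that the study is not powered for bleeding. A larger apparent ratio can be constructed: 0% against 30% discontinuation at uniform times cuts mean treatment time to 0.85 of the planned time in one arm, and 1/0.85 = 1.18. But that also needs an unchanged bleeding hazard after stopping an anticoagulant.
- **That the formula cannot adjust for treatment duration.** With an on-treatment numerator it very nearly does.
- **That stopping treatment at a bleed overstates the rate.** It does not. Overstatement needs a patient to stop first, bleed later and still be counted.

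Bleeding is a secondary endpoint, and the bias is unlikely to change any conclusion of this trial. It is still worth correcting, because the article expects its results to inform larger studies.

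**What to change.** In the Analyses section, define the rate as the number of patients with a first bleed on treatment, divided by on-treatment person-time up to that first bleed or the end of the on-treatment window, whichever is earlier. State what the on-treatment window is. Keep the whole-study frequency table as the summary of all randomized patients, so that bleeds after stopping are still reported.

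The cost is a sentence or two of wording and a little programming, with no new visit or procedure. It relies on the onset date of each bleed and the date of stopping study drug being recorded. The article says only that adverse events are recorded at visits, so the data collection forms should be checked for both dates.

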## Discussion

Despite advances in pharmacological therapy and devices for patients with HF, mortality, both in-hospital and post-discharge, remains high. Ongoing myocardial ischemic damage and hypercoagulability during and after hospitalization might be associated with poor outcomes. A recent prospective trial demonstrated that treatment with low-dose rivaroxaban, a factor Xa antagonist, decreased the rate of stroke or TIA in patients with chronic HF and coronary artery disease with sinus rhythm after a recent worsening episode compared with the placebo (10). This suggests that anticoagulation with factor Xa antagonists might reduce myocardial damage during hospitalization and improve outcomes in patients with ADHF and AF compared with warfarin treatment. ROAD HF-AF is designed to evaluate the potential benefits of rivaroxaban on myocardial and renal damage compared with VKAs, using surrogate biomarkers in hospitalized patients with ADHF and AF.

### Early Effect of Rivaroxaban on Circulating hsTn Levels in Hospitalized Patients With Acute Decompensated HF

Troponin (Tn) level is frequently elevated in patients with ADHF, even without clinically evident coronary artery disease (20). The circulating troponin (cTn) level has been reported to be a reliable prognostic marker for short- and long-term outcomes in patients with ADHF (21, 22). Furthermore, studies on serial cTn measurements throughout hospitalization reported that patients with persistently elevated cTn had a worse prognosis than those without persistently elevated cTn (23). More recently, in a subgroup analysis of the RELAX-AHF study (19), the peak change in hsTn was found to be an independent risk predictor for cardiovascular death or renal injury/HF hospitalization and cardiovascular mortality up to 6 months. We will evaluate the benefit of rivaroxaban compared with VKAs using the peak change in hsTn in patients with ADHF and AF during hospitalization. According to RELAX-AHF study, the peak value of high hsTn was measured at day 2–day 5. Therefore, measuring the maximum change in the hsTn level over 72 h from admission as a primary endpoint would be reasonable.

### Justification for the Extended Therapeutic Intervention and Follow-Up

Studies on the efficacy of novel target drugs, such as ularitide or serelaxin, during short-term hospitalization reported unsatisfactory long-term outcomes in patients with ADHF (24, 25). Furthermore, the results of the ASTRONAUT study, which investigated the change in Tn between the pre- and early post-discharge periods (1 month) in hospitalized patients with ADHF, demonstrated that patients experienced an extended period of vulnerability to cardiac injury after the index hospitalization (26). Therefore, in our study, anticoagulation evaluation in both rivaroxaban and VKAs groups will be continued for 6 months, and the long-term effect will be assessed as a secondary outcome. For example, the serial changes in hsTn and clinical outcomes will be followed up to 6 months. The extended treatment and follow-up assessments are expected to elucidate the long-term efficacy and safety of rivaroxaban. Furthermore, we will evaluate the clinical effect of changes in hsTn during hospitalization and early-discharge on long-term clinical outcomes.

